## Abstract

**Background:**

Allergic diseases in infants have dramatically increased in developed countries during the past few decades. To date, extensive research has been done on risk factors for allergies in infancy, and preventive measures against them. However, the effect of the primary approach to preventing infantile allergy is still limited.

The aim of this trial is to evaluate whether prenatal education interventions, including the latest public research results on allergic diseases, prevent the onset of infant allergies.

**Methods/design:**

We designed a randomized controlled, two-arm (standard prenatal education vs our education), parallel-group, assessor-blind trial. A sample of 120 pregnant women will be recruited at Chiba Aiyu-kai Kinen Hospital and allocation is by computer-generated randomization.

Pregnant women in the intervention arm participate in the childbirth education program established by the specialist and a pediatric allergy educator. The program was developed based on evidences supporting interventions on primary prevention, which are suggested to be beneficial to infantile allergies in recent studies.

The primary objective of the study is to determine whether it is possible to establish effective behaviors for allergy prevention in early infancy in the children of pregnant women who participate in an educational program developed by pediatric allergy specialists. Four months after birth, their behaviors will be compared against those of pregnant women who did not participate in the program.

**Discussion:**

Allergies are common in many individuals worldwide, and can be present from babyhood through the person’s lifetime. One of the strong points of this study is that it should provide pregnant women with accumulated information on preventive knowledge against allergy, that can be effective in some cases, and that women can apply a combination of these behaviors before and after pregnancy. The results of our program will be publicized to help change the behaviors of mothers, and, if the program is effective, for preventing allergies in infants, it will be disclosed worldwide as a new preventive strategy for allergy in infants.

**Trial registration:**

UMIN-CTR, ID: UMIN000034730 Retrospectively registered on 1 December 2018.

## Introduction

In Japan, as in most developed countries, the prevalence of allergy, including atopic dermatitis (AD), food allergy (FA), asthma, and allergic rhinitis, among infants has increased in recent years and is a serious health problem [1]. The “allergic march,” which was first proposed by Minoru Baba, and refers to the chain reaction of allergies in people predisposed to atopic dermatitis [2, 3], has attracted a great deal of attention in recent years, and it has been suggested that preventative measures during the neonatal and early infancy period could be effective against this condition.

To date, extensive research has been conducted on the risk factors for, and preventative measures against, allergy during infancy. In addition, evidence supporting the efficacy of several of these preventative measures has accumulated. For example, in 2008, Lack hypothesized that sensitization to allergens occurs through environmental exposure to allergens through the skin and that consumption of food allergens induces oral tolerance (dual-allergen-exposure hypothesis [4, 5]), and proposed a new allergy-prevention strategy based on the maintenance of skin-barrier function. To verify the dual-allergen-exposure hypothesis, randomized clinical trials (RCTs) of the effects of a moisturizer were conducted, and its efficacy in AD patients was demonstrated [6–8]. Lowe et al. (2016) [9] performed a meta-analysis and showed that a moisturizer can statistically significantly prevent infantile AD when used in the neonatal period, and that the onset of AD is associated with sensitization to egg-white antigen. On the other hand, this analysis suggested that the efficacy of moisturizer alone used from the neonatal period is poor because it cannot prevent sensitization to food allergens.

In addition to the dual-allergen-exposure hypothesis, some studies suggest that maternal intestinal bacterial flora is associated with neonatal allergy [10, 11]. Currently, probiotics [12], prebiotics [13], and synbiotics [14] are effective for the treatment of abnormal intestinal bacterial flora. Some RCTs have examined the effects of probiotic intake by pregnant and lactating women on preventing the development of allergies in infants [15–19]. Zuccotti et al. (2015) [20, 21] performed a meta-analysis on these RCTs, and suggested that probiotic intake in pregnant and lactating women can reduce the incidence of rashes in neonates. However, probiotics did not reduce the prevalence of asthma or allergic rhinitis. A different meta-analysis of RCTs assessing the effects of prebiotics [22] and synbiotics [23] showed that although these organisms prevent the development of a rash, they have no protective effects against allergic sensitization in neonates. Additional studies are needed to assess the differences in intestinal bacterial flora between various races or regions.

Some observational studies identified many risk factors and preventive measures for allergy in infants. An observational study that examined the association between living conditions and infantile asthma [24, 25] reported that the combination of preventive measures to avoid allergens, such as tick and mold, can reduce the risk of allergy. Second-hand tobacco smoke from parents or other family members living together increases the risk of bronchial asthma in infants [26–28]. The association between living conditions and the risk of allergy in infants has been researched extensively. Many observational studies examined the correlation between food intake by pregnant women or lactating mothers and the development of allergies in infants. Specifically, the intake of vitamin D (VD) [29–31] and n-3 polyunsaturated fatty acids [32–34] during pregnancy reduces the risk of allergy in infants. However, there are no recent meta-analyses [35–40] or RCTs [41–46] demonstrating the efficacy of these nutrients against allergies.

The preventive measures reported to date have shown limited effects, and a clear and effective method to prevent allergies in infants remains to be identified. Because multiple risk factors are associated with allergies in infants, the preventive measures identified to date are not effective.

We hypothesized that providing pregnant women with knowledge regarding the latest research findings on allergy prevention in prenatal and postnatal period may increase awareness and knowledge and, thereby lead to changes in behavior to prevent allergy in infants. The aim of this trial is, therefore, to evaluate whether prenatal education interventions, including the latest public research results on allergic diseases, prevent the onset of infant allergies.

This protocol has been written in accordance with the Standard Protocol Items: Recommendations for Interventional Trials (SPIRIT) guideline (Additional file 1). This report is based on protocol version 9, approved 1 March 2019, by Chiba Aiyu-kai Kinen Hospital Ethics Committee.

## Methods/design

### Objectives

#### Primary objective

The primary objective of the study is to determine whether it is possible to establish effective behaviors for allergy prevention during early infancy in pregnant women who participate in an educational program developed by pediatric allergy specialists. Four months after birth, their behaviors will be compared against those of pregnant women who did not participate in the program.

#### Secondary objectives

The secondary objectives are as follows:
To determine whether the use of a moisturizer can reduce the onset of AD and eczemaTo determine whether the onset of other atopic disorders can be prevented by the use of a moisturizerTo examine the association between the onset of AD and food allergy sensitizationTo establish the safety of the recommended moisturizer in neonatesTo investigate the presence of allergies, skin condition, serum immunoglobulin E (IgE), and thymus and activation-regulated chemokine (TARC) levels in neonates

### Trial design

This study is an assessor-blinded, randomized controlled, parallel-group comparison study (comparing our educational program group with an established childbirth education group) conducted in Chiba Aiyu-kai Kinen Hospital (hereafter referred to as “our hospital”) to examine the superiority of the educational program over established programs. Subjects are randomized in a 1:1 ratio into one of the two groups. The participants and study personnel are not blinded with respect to the assignments.

This protocol is written in accordance with the Standard Protocol Item: Recommendations for Interventional Trials (SPIRIT) guideline. Trial registration is through the University Hospital Medical Information Network – Clinical Trials Registry (UMIN-CTR) (UMIN000034730).

### Participants

#### Recruitment procedure

Participants are recruited among all pregnant women who visit our hospital for consultation regarding delivery. The investigator meets with each pregnant woman to provide oral and written information on the study and to request participation. Participants are selected according to the eligibility criteria. The pregnant women discuss participation with their respective families, and those who agree to participate in the study provide informed consent. After the collection of consent forms, the participants are randomized to one of two groups.

#### Eligibility criteria

Eligibility and exclusion criteria are as follows:

Eligibility criteria (individuals must meet two criteria):
Those planning to give birth in our hospitalThose planning to attend the childbirth education program provided by our hospital

Exclusion criteria (any of the following criteria):
Those who were not planning to give birth in our hospitalBirth of triplets or moreChildren with serious congenital malformationsAbnormal birth including fetal distress and neonatal asphyxiaOther pregnant women and neonates assessed as inadequate for the study by a physician

### Intervention

#### Intervention arm

Pregnant women in the intervention arm participate in the childbirth education program established by the specialist and a pediatric allergy educator (PAE). The program was developed based on evidences supporting interventions on primary prevention, which are suggested to be beneficial to infant’s allergies in recent studies. In addition, the intervention groups will receive this program in face-to-face education. In this program, we propose three types of barriers that protect infants from allergy: the intestinal mucosa, the respiratory tract mucosa, and the skin. We then recommend behaviors for mothers that improve the functions of these three types of barriers. Table 1 explains the details of the program using the Template for Intervention Description and Replication (TIDieR) [48], a template for intervention description.

**Table 1 Tab1:** Details of the educational program provided to the intervention arm

Item	Description
1. Brief name	Perinatal education to prevent allergy in infants
2. Why?	Although many parents are anxious regarding allergies and skin conditions in infants [47], there are few opportunities to learn about the prevention of pediatric allergies and skin conditions. Extensive information on pediatric allergy is available based on scientific evidence, and prophylaxis in pregnant women is expected to be effective to prevent allergy in infants. If pregnant women learn how to prevent pediatric allergy based on scientific evidence and apply these principles to childcare, this can promote the establishment of a prophylactic strategy against allergy in infants
3. What materials?	Educational materials for the program were prepared using PowerPoint. A handbook with illustrations and photographs reviewed by a specialist is provided to mothers to educate them about proper skin care for infants and the optimal diet during pregnancy and *lactation*
4. What procedures?	A session planned during early and late pregnancy consists of the following: ➢ Program in Early pregnancy Title: What you can do for your baby Subtitle: Advice from pediatric allergy specialists Intestinal mucosa ✓ Effect of the maternal intestinal bacterial flora on the fetus ✓ A diet that includes nutrients (oligosaccharides, dietary fiber, and fermented food) is ideal for pregnant women to regulate for healthy intestinal bacterial flora ✓ Effect of vitamin D and a diet that includes vitamin D ✓ Effect of n-3 polyunsaturated fatty acids and a diet that includes this acid Skin ✓ Association between the skin of infants and sensitization to allergens ✓ Adequate exposure to ultraviolet light Respiratory tract mucosa ✓ Effect of smoking on pediatric bronchial asthma ➢ Program in Late pregnancy Title: What you want to know for your baby? Subtitle: Advice from specialists on pediatric allergy: “Three barriers protecting our body” Intestinal mucosa (the same content as in Program in Early pregnancy) Skin ✓ Association between the skin of infants and sensitization to allergens ✓ Differences between the skin of infants and that of adults ✓ Prevention of allergic dermatitis and proper skin care starting at the neonatal period ✓ Proper skin care for neonates (how to wash and moisturize the skin) ✓ Proper exposure to air Respiratory tract mucosa ✓ Effect of smoking on pediatric bronchial asthma ✓ Risk of exposure of infants to allergens in the living environment, in particular in bedclothes ✓ Cleaning bedclothes and the living areas of infants
5. Who provides?	Specialist or educator of pediatric allergy
6. How?	Face-to-face group learning
7. Where?	Chiba Aiyu-kai Kinen Hospital where pregnant women are planning to give birth
8. When?	Two 90-min sessions (at approximately 20 and 30 weeks of pregnancy)
9. Tailoring	Not individualized
10. Modifications	Any changes occurring during the study period need to be reported
11. How well?	Plan: To promote adherence to the recommended skin care practices among subjects participating in the educational program. A moisturizer is provided free of charge to those who want to use it
12. How well?	Practice: Strategies to promote adherence to skin care practices will be reported in a paper

### Control arm

A leaflet summarizing the content of the educational program that is provided to the intervention arm is made available to subjects in the control arm at approximately 20 and 30 weeks of pregnancy.

### Measurements/assessments

#### Primary outcomes

##### Self-evaluation of questionnaire to identify the behavioral characteristics of mothers based on the educational program at 4 months after delivery

Primary outcomes are evaluated according to a self-evaluation score at 4 months after delivery in both arms.

The score is determined using a survey sheet created for this study (Appendix) to assess the behavioral characteristics of mothers. We prepared 21 questions to assess the dietary habits of mothers, living conditions, and the skin care of children based on the ideal behavior of mothers to prevent allergy in infant as proposed by specialists. Five options (a–e) are provided for all questions: a = 1, b = 2, c = 3, d = 4, and e = 5. Higher scores indicate more appropriate behaviors of mothers to prevent pediatric allergy at each time point.

#### Secondary outcomes

We set the following seven secondary outcomes:
Incidence and severity of atopic dermatitis and eczema infantile

The incidence and severity of AD and eczema in infants aged 1 week, 1 month, 4 months, and 12 months are determined by a “blinded” pediatrician according to the Clinical Practice Guidelines for the Management of Atopic Dermatitis 2016 prepared by the Japanese Dermatological Association: URL:https://www.dermatol.or.jp/uploads/uploads/files/guideline/atopicdermatitis_guideline.pdf.
2.Incidence of food allergy and sensitization to egg white, milk, and ovomucoid

The incidence of food allergy in infants aged 4 and 12 months is determined by sensitization using serum antigen-specific IgE [49], medical interview, and oral food challenge or a clear history of allergy triggered by accidentally ingested foods
3.Analysis of stratum corneum hydration, transepidermal water loss (TEWL), and microscopic and digital images

Stratum corneum hydration in infants is measured three to five times on the left lower leg, forehead, and left cheek using Skicon-200EX® (IBS Japan Co., Ltd., Shizuoka, Japan). TEWL is determined two to three times on the left lower leg, forehead, and left cheek using the VapoMeter® (DelfinTechnologies, Kuopio, Finland). Enlarged images of the skin of the left lower leg, forehead, and left cheek in infants are acquired using a USB microscope M3 (Scalar Corporation, Tokyo, Japan). Images of a wide range of skin surfaces in infants are obtained using a digital camera (Canon, Tokyo, Japan). The skin is measured and photographed at 22 °C and 50% humidity.
4.TARC level

Serum TARC level is measured in infants aged 4 and 12 months to assess the severity of AD
5.Frequency of use and amount of moisturizer

The total amount of moisturizer used during the study is calculated to predict the effect of the educational program. The moisturizer is provided free of charge to those who want to use it
6.Questionnaire survey on living habits, awareness, and knowledge of mothers before and after pregnancy

A questionnaire survey on living habits, awareness, and knowledge of mothers before and after pregnancy was prepared. Subjects answer the self-evaluation questions in the survey at 30 weeks of pregnancy, and at 1, 4, and 12 months after delivery. Questions on living habits address stool frequency, use of supplements, eating habits between meals, and foods avoided or foods eaten. Regarding awareness and knowledge, the questions address what the mothers care about before and after pregnancy, how they intend to provide nourishment for the baby, and their concerns regarding childcare and the skin care of the baby.
7.Adverse events

Self-reported adverse events associated with the use of the moisturizer provided free of charge to those who want to use it during the study are recorded.

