### Participant timeline

Table 2 shows the consent forms obtained from the subjects, the intervention, and the evaluation schedule.

**Table 2 Tab2:** Consent, enrolment/allocation, and assessment of subjects (Additional file 2)

	Study period							
	Enrollment Allocation	Post allocation						
Time point	Early pregnancy	20 weeks of pregnancy	30 weeks of pregnancy	Delivery	Discharge	1 month after delivery	4 months after delivery	12 months after delivery
Enrollment/allocation:								
Inclusion	●							
Obtaining informed consent	●							
Randomization	●							
Baseline survey		●						
Interventions:								
Educational program		●	●					
Established childbirth education		●	●					
Assessments:								
Questionnaire survey on living habits, awareness, and knowledge of mothers before and after pregnancy			●			●	●	●
Survey on the behavioral characteristics of mothers						●	●	●
Blood collection from mothers	●		●					
Blood collection from infants (IgE and TARC)							●	●
Stratum corneum hydration of infants					●	●	●	
TEWL of infants					●	●	●	
Findings on the skin of infants (scoring atopic dermatitis (SCORAD)) [50]					●	●	●	
Images of the skin of infants					●	●	●	
Diagnosis of atopic dermatitis in infants							●	●
Diagnosis of food allergy in infants							●	●
Provision of moisturizer					●	●	●	
Collection of the moisturizer container						●	●	●

Legend: *IgE* immunoglobulin E, *SCORAD* scoring atopic dermatitis, *TARC* thymus and activation-regulated chemokine, TEWL transdermal water loss

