#### Frequency of use and amount of moisturizer

Descriptive statistics of the total amount of moisturizer and rate of changes in the scores at each time point are calculated and compared between groups. An evaluation is performed considering birth month as a baseline characteristic.

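### The moisturizer safety objective cannot be met by its only designated outcome, which counts self-reported events already classed as linked to a voluntarily used product

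*Protocol article*

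**What the plan says.** The fourth item under Secondary objectives is to establish the safety of the recommended moisturizer in neonates. Under Secondary outcomes, the protocol announces "We set the following seven secondary outcomes", and the seventh, Adverse events, is the only one that addresses this objective. It is defined as "Self-reported adverse events associated with the use of the moisturizer provided free of charge to those who want to use it".

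Three other statements bear on how that outcome will behave:

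- **Blinding.** Trial design states: "The participants and study personnel are not blinded with respect to the assignments". The mothers who report events therefore know their arm.
- **Exposure.** Use is by choice: "The moisturizer is provided free of charge to those who want to use it". The program description in Table 1 lists the same offer as a measure to support adherence to skin care.
- **Use by arm.** The total amount is measured and analysed in both arms: "Descriptive statistics of the total amount of moisturizer and rate of changes in the scores at each time point are calculated and compared between groups".

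Infant skin is also examined independently of what the mother reports. Secondary outcome 1 has a blinded pediatrician determine AD and eczema at 1 week and at 1, 4 and 12 months. The analysis section compares their incidence between groups. Table 2 schedules SCORAD at discharge, 1 and 4 months. None of this is designated as safety data.

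**The concern.** The objective and the outcome do not match. The objective asks for a conclusion about safety. The outcome lets an event in only after it has been linked to one product. Rash, dryness and irritation also occur in infants who use no moisturizer, so a rate among users can be interpreted only against all such events, whatever their presumed cause. A definition that screens on association before recording removes that reference, and no later analysis plan can recover events that were never written down.

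The reports come from mothers who know their arm and who chose to use the product. The document names no one who decides whether an event is associated with the moisturizer. If few events are recorded, the trial cannot tell whether few occurred or whether few were reported and linked. What is at stake is a statement about product safety in newborns that the data would not support.

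**Working it through.** The document gives no event rate, safety margin or number of exposed infants, so there is no safety figure to reproduce. The sample size of 60 per group was set for the questionnaire score. The check has three steps.

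**1. Objective against outcome**

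- Objective (Secondary objectives): establish safety in neonates.
- Outcome (Secondary outcomes, item 7): events that are self-reported, classed as associated with the moisturizer, and concern the free product.
- Result: an event in a user that nobody links to the product falls outside the outcome, as does every event in a non-user. No denominator is defined. The only background rate available is for AD and eczema, through secondary outcome 1.

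**2. What zero events could exclude with complete capture**

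With 0 events in n exposed infants, the exact one-sided 95% upper limit is 1 − 0.05^(1/n). The two-sided 95% interval ends at 1 − 0.025^(1/n). Uptake is not stated, so n is an assumed range up to the planned total of 120, counting one infant per woman.

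| Exposed infants (assumed) | One-sided upper limit | Two-sided upper limit |
|---|---|---|
| 30 | 9.5% | 11.6% |
| 60 | 4.9% | 6.0% |
| 90 | 3.3% | 4.0% |
| 120 | 2.5% | 3.0% |

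The 120 row requires every participant to take up the product.

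**3. What incomplete capture adds**

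This step is an illustration with assumed inputs: 60 exposed infants, true event rate p = 5%, and a share s of events that is both reported and classed as associated. The probability of recording no event is (1 − p·s)^60.

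- s = 1: 0.95^60 = 4.6%
- s = 0.5: 0.975^60 = 22%
- s = 0.25: 0.9875^60 = 47%

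With full capture, a clean record would be unusual at a true rate of 5%. If a quarter of events are captured, it happens almost half the time. The document gives no value for s, and the outcome as defined provides no way to estimate it.

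**The case against.** The strongest reply is that the document has more safety-relevant data than item 7, and that much of what seems absent may only be condensed. Several stronger readings are tempting and do not hold:

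- **Mothers report spontaneously and judge the cause themselves.** The text says neither. Self-report can be elicited, and no one is named as judge of association. What stands is that the outcome is filtered by association.
- **Events are not collected on schedule and not compared between arms.** Table 2 has a row for "Collection of the moisturizer container" but none for adverse events, and the analysis section covers the other six secondary outcomes only. A journal article may leave such detail to the full protocol or analysis plan, so this silence is not counted as a defect.
- **A rash put down to baby eczema would never be recorded.** The blinded assessment of AD and eczema contradicts this. It records such cases in both arms whatever the mother thinks. It does not cover other reactions.
- **Reporting must be biased between arms because one arm is taught to trust moisturizing.** The control arm receives a leaflet summarizing the same content. Reporting could still differ by arm, but any figure for the difference would follow only from assumed inputs.
- **A comparison by randomized arm would settle safety.** Moisturizer use is voluntary and recorded in both arms. A contrast between arms would reflect the education program and the choice to use the product, not the product alone.

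It is also fair to say that this is one of five secondary objectives, and that nothing in the document says a low count would be reported as proof of safety. These points narrow the concern. They do not remove the mismatch between an objective to establish safety and an outcome that screens events by presumed association.

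**Conclusion.** The concern holds in this limited form: the designated outcome cannot establish the safety of the moisturizer. It gives no background rate for reactions other than AD and eczema, and a low count is compatible with both safe use and missed events.

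Even under the favourable assumption of complete capture, zero events leaves true rates of up to about 2.5% (120 exposed), 4.9% (60) or 9.5% (30) unexcluded at one-sided 95% confidence. These limits depend on an uptake that the document does not state. The probabilities under partial capture rest on an assumed 5% event rate and assumed capture shares, and show direction only.

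The problem rests on the stated definition and not on what the article leaves out. It concerns a secondary objective and has no effect on the primary analysis. It deserves correction because a claim about neonatal safety should not rest on this outcome and because the change is cheap.

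**What to change.** - **Outcome (Secondary outcomes, item 7).** Record all skin and other adverse events in every infant in both arms, whatever the presumed cause. Use one standard question at the existing discharge, 1-, 4- and 12-month visits, and show it in Table 2.
- **Reporting.** Give incidence with 95% confidence intervals among infants who used the moisturizer, with that number as denominator; use is already recorded. Show non-users and the randomized arms descriptively, and state that use is not randomized. Read the results alongside the blinded AD and eczema findings and SCORAD.
- **Relatedness.** If a judgement of relation to the moisturizer is wanted, name who makes it, and choose someone other than the blinded assessor of AD and eczema. Telling that assessor about moisturizer use could reveal the arm.
- **Objective (Secondary objectives, fourth item).** Reword it as describing adverse events, and report the upper limit that the number exposed can exclude.

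The cost is one question at visits that already take place, one table row and a reworded objective. More unrelated minor events will be recorded, and the safety statement becomes more modest.
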